## Abstract

**Background:**

Major lower extremity amputations are frequently performed for end-stage peripheral arterial disease and progressive diabetic foot complications. Wound complications after amputation affect up to one-third of limbs. The patient cohort undergoing amputation are typically high risk for poor wound healing, often with unmodifiable risk factors in an urgent clinical setting. Incisional negative pressure wound therapy (NPWT) has been shown to reduce wound complications in other high-risk populations. This randomized controlled trial investigates whether prophylactic NPWT reduces wound complications in patients after major amputation compared with standard dry dressings.

**Methods:**

This protocol describes a prospective, multicentre, randomized controlled trial with an internal pilot recruiting patients undergoing major lower extremity amputation for any indication. Limbs will be randomized to receive either a single-use NPWT device on their closed surgical incision or a dry dressing. The primary clinical outcome is the rate of wound complications. Secondary outcomes include reoperation rates, length of hospital stay, cost-effectiveness of NPWT, and patient-reported quality of life. Follow-up will continue to 6 months after surgery. The initial pilot phase has a recruitment target of 96 limbs, whereas an estimated 728 patients will be required to power a definitive trial adequately.

**Discussion:**

This trial aims to supplement the existing poor-quality data on this important aspect of care and equip healthcare professionals to make cost-effective decisions regarding postoperative wound management.

## Background

Major lower extremity amputations are frequently performed for unreconstructable peripheral arterial disease and progressive diabetic foot complications^1,2^. As the population ages and the prevalence of diabetes increases, rates of diabetic-related major amputations are projected to increase despite advancing revascularization techniques. In both the UK and Ireland, rates of major amputation are significantly higher in the diabetic population^3,4^. In the United States, approximately 185 000 major amputations are performed annually, and the number of patients living with limb loss is projected to double from 1.5 million to 3.6 million by 2050^5^. Up to one-third of patients experience perioperative wound complications after major amputation^6–10^. Conversion from below-knee amputation (BKA) to above-knee amputation (AKA) is estimated to occur in 12–34% of limbs, with wound infection causative in a significant number of cases^8^. The 30-day readmission rate after a lower extremity amputation ranges from 29 to 46%^9,11^. Prolonged inpatient stays, multiple procedures, costly comorbidities, and high rates of readmissions lead to patients with peripheral arterial disease accumulating hospital costs six times those of general inpatients^12^. Similarly, the healthcare costs and resource utilization of diabetic foot care in England is greater than the combined cost of breast, prostate, and lung cancers^13^.

Many factors influence the risk of wound complications^14–18^. Notably, the presence of proximal occlusive arterial disease is a major influence on stump healing. Patient factors such as smoking, diabetes, obesity, malnutrition, and chronic kidney disease are non-modifiable, particularly in the emergency setting. However, surgical factors may be altered in an effort to reduce the risk of wound complications. One variable amenable to alteration is what dressing is applied to the closed incision upon procedure completion. The type of dressing may influence factors such as bacterial access to the wound, the development of collections of blood or fluid within the wound bed, or discharging onto the wound edges. Collectively, these wound factors increase the risk of wound infection. Therefore, dressings that reduce these factors have the potential to reduce wound breakdown, thereby reducing the burden for patients and healthcare systems.

## Trial rationale

Negative pressure wound therapy (NPWT) has been used successfully to treat a variety of complex wounds^19^. The technology has been adapted into single-use battery-powered dressings designed for closed surgical incisions rather than cavitating, open wounds. These NPWT dressings consistent of an open-cell solid foam, placed on top of the incision and then covered with a semipermeable membrane. A sealed tube connects the foam to a pump to create a partial vacuum over the wound. This negative pressure leads to a sealed environment that prevents bacterial migration into the wound while removing blood and serous exudate. The systems can be applied and, once sealed, left in place for up to 7 days. Single-use NPWT systems (Smith & Nephew’s PICO™ and Acelity’s Prevena™) are now widely available.

Prophylactic NPWT in the setting of closed surgical incisions has been widely evaluated. A recently updated Cochrane review (2022) analysed data from 62 randomized controlled trials (RCTs) and six economic studies, including 13 340 participants across a range of surgical specialities (gastrointestinal, gynaecological, vascular, orthopaedic, and cardiothoracic)^19^. The review was concluded with moderate certainty that prophylactic NPWT reduces the incidence of surgical site infection (SSI) though not wound dehiscence. Nonetheless, it should be noted that the definition of SSI varied amongst included studies. As such, it remains unclear whether NPWT reduces all wound infections, just superficial infections alone, or deep infections.

Stemming from this first success, the role of NPWT has been investigated across specialities and anatomical locations. In vascular surgery, the majority of the literature has focused on vascular groin exposures, an area known to be high risk for wound infection and breakdown due to a constellation of patient and wound factors. A meta-analysis^20^ of eight RCTs with 1125 patients reported an overall reduction in SSI rates but no difference in wound dehiscence, seroma formation, and reoperation and readmission rates. Lower extremity amputations are another wound bed vulnerable to deterioration; however, the literature^21^ investigating the impact of incisional NPWT on amputations is limited and underpowered.

To answer these outstanding questions, a multicentre RCT (“PINTA”) is proposed comparing prophylactic single-use NPWT with standard dressings in patients with a closed incision following an lower extremity amputations.

## Objectives

The single main research question for this trial is as follows: in adult patients with major amputations, do single-use NPWT devices reduce post-operative wound complications?

### Primary objective

The primary objective for the trial is to quantify and analyse differences in the rates of composite wound complications at 30 days after amputation between NPWT and standard dressings. Wound complications are defined as infection, either deep or superficial; wound dehiscence, either partial (fascia intact) or complete (fascia breached); seroma; haematoma; and wound necrosis.

### Secondary objectives

The secondary objectives comparing standard dressings with NPWT dressings are as follows:

To determine and analyse any difference in SSI rates;To determine and analyse any difference in wound dehiscence rates;To determine and analyse any difference in length of stay from surgery to discharge from acute hospital, not including subsequent days spent in step-down care of an equivalent setting;To determine and analyse any difference in readmission rates for wound-related complications in the 6 months following major amputation;To quantify and analyse differences in patient-reported general health-related quality of life in the 6 months following major amputation;To quantify and analyse differences in patient-reported wound-related quality of life in the 6 months following major amputation;To quantify and analyse differences in patient financial impact in the 6 months following major amputation;To determine the number and nature of further interventions related to amputation in the first 6 months following the index procedure;To investigate resource use and thereby cost-effectiveness of single-use, prophylactic NPWT devices *versus* standard dressings for closed-incision amputation wounds.

## Trial design and endpoints

### Statement of design

This is a prospective randomized controlled, assessor-blinded trial, with participants allocated to one of two parallel arms in a 1 : 1 fashion. The primary trial centre is University College Hospital Galway, Ireland, and other Irish centres being evaluated include University Hospital Limerick, University Hospital Waterford and, in Dublin, St James University Hospital, St Vincent’s University Hospital, Tallaght University Hospital, and Beaumont Hospital. All adult patients presenting at trial centres in an inpatient or outpatient capacity requiring a lowet extremity amputation suitable for primary closure are potentially eligible for inclusion. The study pathway is outlined in *Fig. 1*.

**Fig. 1 zraf159-F1:**
[figure not shown]
PINTA study pathway including treatment arms and follow-up intervals NPWT, negative pressure wound therapy; EQ-5D-5L, patient quality of life questionnaire; Wound-QoL, patient chronic wound quality of life questionnaire; CoPaQ, cost for patients questionnaire; CRF, case report form.

The trial will be conducted at Irish tertiary vascular centres over a period of 3 years. Participating patients will have a clinical follow-up at the centre’s surgical outpatients department for a minimum of 6 months. This is standard clinical practice for all specialties following these types of procedures. At 1, 3, and 6 months after amputation, patients will complete the quality of life (EQ-5D-5L^TM^), chronic wound quality of life (Wound-QoL^TM^), and cost for patients (CoPaQ^TM^) questionnaires to evaluate the functional and financial impact of amputation and amputation-related complications on the patients. Late complications and surgical interventions related to their index procedure will also be collected to evaluate the financial impact on the healthcare system.

### Outcomes

#### Primary efficacy outcome

The primary outcome measure is any wound complication of the amputation stump, including SSI, dehiscence, seroma, haematoma, and stump necrosis. The Centre for Disease Control and Prevention^14^ definitions of SSI will be used (*Appendix 1*). As part of trial on-boarding, the Centres for Disease Control and Prevention (CDC) criteria for SSI will be shared to all clinicians involved in patient assessment. The treating clinical team will make the diagnosis of wound infection, as per routine clinical practice. Given that prompt diagnosis and treatment of wound infection is a core part of routine clinical care, the treating clinicians will typically document such a management change in the patients’ medical records. In addition, an independent outcome assessor will review data collected in the clinical report forms to confirm the diagnosis of a wound complication. For the purposes of the trial, any wound infection requiring ongoing medical intervention or that has led to reoperation at or after 30-day review will be considered a deep infection. Furthermore, any dehiscence involving the fascia or requiring interposition vacuum-assisted closure (VAC) therapy will be considered a deep dehiscence. Similarly, any stump necrosis involving the fascia or deeper structures will be considered deep necrosis, whereas superficial necrosis will be confined to the skin and subcutaneous tissues.

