### Device assessment

The single-use NPWT device will be reviewed daily by the surgical team and issues with sealing and exudate will be recorded. The number of devices left *in situ* sealed appropriately for the recommended period (minimum 5 and maximum 7 days) will be noted. All episodes of resealing on the ward will be documented. Reasons for premature removal of the NPWT device will be recorded.

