#### Wound assessment

The surgical incision will be reviewed by the clinical team as appropriate while the patient remains in hospital. All incidences of wound complications will be documented prospectively. The presence of SSI will be determined using the CDC criteria. The time taken in days from surgery to wound healing will be recorded. At 30 days, the surgical incision will be reviewed by a surgeon blinded to the initial wound management strategy and categorized as ‘healed’ or ‘not healed’.

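### The reading expressly made blind (healed or not healed at 30 days) is not the primary composite, whose infection component is diagnosed by a treating team that cannot be blind

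*Protocol article*

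**What the plan says.** All places are in the Protocol article.

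- **Statement of design:** "This is a prospective randomized controlled, assessor-blinded trial".
- **Primary efficacy outcome:** "The primary outcome measure is any wound complication of the amputation stump, including SSI, dehiscence, seroma, haematoma, and stump necrosis". The Statistical analysis section analyses this as the proportion of patients with any such complication at 30 days.
- **Primary efficacy outcome, on infection:** "The treating clinical team will make the diagnosis of wound infection, as per routine clinical practice". The section then adds a second step: "an independent outcome assessor will review data collected in the clinical report forms to confirm the diagnosis of a wound complication".
- **Wound assessment:** "The surgical incision will be reviewed by the clinical team as appropriate while the patient remains in hospital". Complications are to be documented prospectively; the section does not say by whom. For the day-30 visit, "the surgical incision will be reviewed by a surgeon blinded to the initial wound management strategy and categorized as" one of two states: healed or not healed.
- **Randomization:** there is no sham.
- **Device assessment:** "The single-use NPWT device will be reviewed daily by the surgical team".
- **Statistical analysis:** the statistician is blinded.

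**The concern.** In an open trial, a claim of assessor blinding is what protects a judgement-dependent endpoint. Superficial infection, seroma and superficial necrosis all leave room for judgement. If staff who know the dressing apply even slightly different thresholds in the two arms, or record events with different completeness, that difference enters the estimated treatment effect directly. A larger sample does not correct it, and blinding the statistician acts too late, because the data are already fixed by then. What is at stake is whether a difference in the primary outcome, or its absence, can be attributed to the dressing.

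**Working it through.** **Step 1. Who determines what, and is that person blind?**

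| Role | What the role contributes | Blinding in the article |
|---|---|---|
| Treating clinical team | Diagnoses wound infection; reviews the incision in hospital | Not stated; cannot be blind (no sham, device reviewed daily) |
| Independent outcome assessor | Confirms wound complications from report-form data | Called independent; blinding not stated |
| 30-day surgeon | Healed or not healed | Expressly blinded |
| Statistician | Analysis | Expressly blinded |

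The expressly blinded clinical reading is not the variable in the primary analysis. Nor can it stand in for that variable: an infection or seroma that arose and resolved before the visit could be classed as healed.

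The sentence about the treating team's diagnosis covers infection only. For dehiscence, seroma, haematoma and necrosis, the article says that the clinical team reviews the incision and that complications are documented. That these components also originate with the treating team is a reasonable inference, not a statement in the text.

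**Step 2. Reproduce the planned sample size.** Inputs from the Sample size section: 25% v 15%, 90% power, 5% significance (two-sided, from Statistical analysis).

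n per arm = (0.25×0.75 + 0.15×0.85) × (1.960 + 1.282)² / 0.10² = 0.315 × 10.507 / 0.01 = 330.98, so 331, as stated. Then 2 × 331 × 1.10 = 728.2, matching 728. The figures are sound and are used only as inputs below.

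**Step 3. Illustrate unequal recording when there is no true effect.** The article gives no recording rates, so those used here are assumptions. True rate 25% in both arms, 331 per arm, no false positives.

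Observed rate = 0.25 × share of events recorded. SE = √{[pC(1−pC) + pN(1−pN)]/331}. Chance of a significant result favouring NPWT = Φ(difference/SE − 1.96).

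- 95% recorded in control, 85% in NPWT: 23.75% v 21.25%; difference 0.025; SE 0.0324; ratio 0.771; Φ(−1.189) = 0.117, about 12%.
- 95% v 80%: 23.75% v 20.0%; difference 0.0375; SE 0.0321; ratio 1.168; Φ(−0.792) = 0.214, about 21%.
- Equal recording: 2.5%.

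**Step 4. The opposite direction.** By symmetry, recording 85% of control and 95% of NPWT events gives about a 12% chance of a false finding for control. With the planned true effect (25% v 15%) it hides benefit:

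- 95% recorded in both arms: 23.75% v 14.25%; SE 0.0303; ratio 3.138; power Φ(1.178) = 88%.
- 85% control, 95% NPWT: 21.25% v 14.25%; difference 0.070; SE 0.0296; ratio 2.367; power Φ(0.407) = 66%.
- 80% control, 95% NPWT: 20.0% v 14.25%; difference 0.0575; SE 0.0292; ratio 1.969; power Φ(0.009) = 50%.

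**The case against.** The plan is not without safeguards. It adopts CDC criteria for infection and shares them with assessing clinicians, adds independent confirmation, and has a blinded 30-day review. The design statement can reasonably be read as covering the independent assessor, and the layout of the forms and the adjudication procedure are details an article may leave to the full protocol. This has weight: the text supports saying that this assessor's blinding is not stated, not that the assessor is unblinded.

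Three stronger readings are tempting and are not supported:

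- *Missed events are never found.* The article does not say whose forms the assessor reads or that only positive cases are passed on. What stands is that a confirming role cannot be relied on to recover unrecorded events.
- *The assessor's forms reveal the allocation.* Device and dressing details are recorded in the trial, but nothing says those fields reach the assessor. Masking is simply not described.
- *Wounds are watched more closely in one arm.* The provision for incision review as appropriate applies to both arms, and the daily review is a check of the device for sealing and exudate. The article sets no different wound surveillance by arm.

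The recording rates in the illustration are assumed and cannot by themselves establish how serious the problem is.

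What survives is the mismatch itself: the expressly blinded reading is a different variable from the primary outcome.

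**Conclusion.** The point holds in this form. The blinding that the article expressly assigns to a clinical assessor covers a variable that the primary analysis does not use. The infection component is diagnosed by staff who know the allocation, and the other components probably originate with them too. The intermediate safeguard, the independent assessor, is of unstated blinding and limited reach. The primary result is therefore open to detection bias.

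Neither the size nor the direction of that bias can be derived from the article. A reader might infer that the trial is biased towards NPWT; the text does not show that. On the assumed recording rates, a gap of 10 to 15 percentage points in completeness raises the one-directional false-positive risk from 2.5% to about 12–21%. The same gap reversed cuts power under the planned effect from 88% to about 66–50%. These figures show sensitivity to unequal recording and do not predict it. That the treating team is not blind is inferred from the absence of a sham and the daily device review, but the inference is strong.

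**What to change.** Use the two assessors already planned.

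1. At the 30-day review, the blinded surgeon rates each component of the composite as well as healed or not healed.
2. State that the independent assessor is blinded and works from an extract with allocation, device and dressing fields removed. This assessor adjudicates every team-recorded event, plus every patient who is not healed at 30 days, received antibiotics for the stump, or was reoperated.
3. Make the adjudicated composite the primary outcome, and report the team-diagnosed composite as a sensitivity analysis.

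**Cost:** a longer 30-day form, a masked data extract and more cases to adjudicate. No change to the sample size follows.

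**Limit:** the change reduces the bias but does not remove it. Events that resolve before day 30 are still known only from unblinded records. Of the adjudication triggers, only the not-healed reading is itself blinded; antibiotics, reoperation and team-recorded events remain decisions of staff who know the allocation. The trial report should say so.

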#### Primary safety outcome

The primary safety endpoints in the intervention group are any complications arising from the additional use of NPWT devices and the requirement for subsequent acute or subacute reintervention (at any time) as a result of the primary intervention.

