### Interventions

#### NPWT

Negative pressure dressings use an open-cell foam laid on top of the wound, which is then covered with an impermeable adhesive membrane. A sealed tube punctures the membrane to connect the dressing in-built pump, leading to the creation of a partial vacuum over the wound. The device is licensed to stay *in situ* and sealed for 5–7 days. In some cases, depending upon the treating surgeon’s normal practice and the volume of wound exudate, the wound may be redressed again on the ward. The postoperative day that the dressing was first removed will be recorded, as will the application of any subsequent NPWT dressings or dry dressings. For the purpose of this trial, NPWT device(s) may be used for up to 14 days after surgery.

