#### Standard dressing

Standard dressing for an amputation wound comprises a non-adhesive layer applied directly to the wound, covered by a sealed dressing, supplemented with protective padding. Such standard dressings do not use negative pressure. The precise details of the materials used will be at the discretion of the treating surgeon as per their routine practice but the details of each dressing applied in the trial will be noted. The duration that each dry dressing is left *in situ* varies between surgeons, though the majority will leave the first dressing for a minimum of 48 hours and a maximum of 5 days. For the purpose of this trial, the type and duration of control dressing will be recorded, including the postoperative day the dressing was first removed.

Of note, it is some surgeons’ usual practice to use a drain in the amputation stump delivered out through a separate incision to protect against haematoma formation; the drain is usually ready for removal at 48–72 hours after surgery. There is a lack of high-quality evidence supporting drain use after major amputation; however, it a widespread practice. Achieving a durable seal for NPWT around a drain can be technically challenging, and a seal may be lost once the drain is removed; extra care should be taken to maintain a seal once the drain is removed. For the purpose of this study, surgeons should not alter their regular practice regarding drain use. The presence or absence of a wound drain will be recorded in the procedural data, allowing for potential subanalysis of the impact of drain use on outcomes.

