### Crossovers

Any crossovers between treatment groups shall be highlighted and reported in the final report. Participants’ follow-up data will continued to be recorded on an intention-to-treat basis, as such patients will continue to be analysed in the group they were originally randomized to whether they received the correct intervention or not. Reasons for protocol deviation will be documented in the site logs, for example NPWT device unavailable or unable to achieve seal despite multiple attempts or surgeon preference. Patients in the control group with unhealed wounds after the initial 14-day review period for whom the treating surgeon feels may benefit from application of a single-use NPWT device will be offered one.

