## Safety parameters

### Potential adverse events related to intervention

Primary safety endpoints include adverse events related to the use of single-use NPWT devices. The risk of any significant adverse event occurring is deemed unlikely; however, all reasonable measures to avoid these events will be undertaken. Any adverse events will be recorded and reported in any trial data, namely local reactions to the NPWT device.

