### Event reporting

Any safety concerns arising with the used of the NPWT dressings should be reported to the Health Protection Regulatory Authority via the online reporting system https://www.hpra.ie/homepage/about-us/report-an-issue/mdiur or by email to [contact]. The sponsor should be notified. Any local hospital procedures in place for reporting safety concerns should be followed.

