Use of randomization by stratification should ensure balance in the recruiting centre in both treatment groups. Whereas clustering effects are not expected to be important for this study, in reality the data may be hierarchical, with patients naturally clustered into groups by recruiting centre. This will be accounted for by generalizing the conventional linear (fixed-effects) regression approach to a mixed-effects logistic regression analysis. This model will be used to assess differences in wound complication rates between the study intervention groups, with results presented as odds ratios with associated 95% confidence intervals. The mixed-effects model will include a random effect to account for any heterogeneity in response due to the recruitment centre and fixed effects to adjust for vascular status. An identically structured and formulated mixed-effects linear regression model will be used to assess the effects of the interventions on secondary outcomes and EQ-5D-5L (at 1, 3, and 6 months) that, for the purposes of analysis, will be assumed to be approximately normally distributed. Other dichotomous outcome variables, such as complications related to the trial interventions, will be analysed in the same manner as the primary outcome. Temporal patterns of any complications will be presented graphically, and, if appropriate, a time-to-event analysis (Kaplan–Meier survival analysis) will be used to assess the overall risk and risk within individual classes of complications. All reported tests will be two-sided and considered to provide evidence for a significant difference if *P*-values are less than 0.05 (5% significance level. Results from this trial will also be compared with results from other trials and reported in accordance with CONSORT guidelines. Whereas there are a multiplicity of secondary outcomes, considering CONSORT guidelines and regulatory body preferences, the authors do not plan to adjust for type 1 errors due to the high risk of a corresponding increase in type 2 errors^22^.

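### Local dressing harms are defined for the NPWT arm only, so the trial as written gives no fair randomised comparison of them

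*Protocol article*

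**What the plan says.** All places are in the Protocol article.

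- **Primary safety outcome:** "The primary safety endpoints in the intervention group are any complications arising from the additional use of NPWT devices". The same sentence adds reintervention resulting from the primary intervention.
- **Potential adverse events related to intervention:** "Any adverse events will be recorded and reported in any trial data, namely local reactions to the NPWT device". The sentence opens broadly, but its last clause narrows it to the device.
- **Standard dressing:** for the dry dressing, "the type and duration of control dressing will be recorded, including the postoperative day the dressing was first removed". No local skin complication is listed.
- **Statistical analysis:** "Other dichotomous outcome variables, such as complications related to the trial interventions, will be analysed in the same manner as the primary outcome". That manner is a mixed-effects logistic regression giving an odds ratio between arms with a 95% confidence interval.
- **NPWT:** "NPWT device(s) may be used for up to 14 days after surgery".
- **Crossovers:** "Patients in the control group with unhealed wounds after the initial 14-day review period for whom the treating surgeon feels may benefit" will be offered a single-use device.
- **Discussion:** tolerability is among the stated aims, and an unsealed device that macerates the wound edges is given as a practical pitfall.

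Two other sections also mention only NPWT, but they carry less weight. Device assessment ("The single-use NPWT device will be reviewed daily by the surgical team and issues with sealing and exudate will be recorded") is about how the device performs. Event reporting ("Any safety concerns arising with the used of the NPWT dressings should be reported to the Health Protection Regulatory Authority") is the regulatory route for device concerns, not outcome collection.

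**The concern.** Maceration, blistering and skin reaction can occur under any dressing on an exuding stump. Counting them only under NPWT gives a rate that mixes three sources: the device, the stump, and the fact of being dressed at all. The randomised control arm is what could separate them, and the text does not say that these events are recorded there.

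What is at stake is the tolerability aim. A reader of the final report would see local reactions for NPWT and nothing to set beside them. If dry-dressing events were noted less completely, a between-arm odds ratio would tend to make NPWT look harmful even with no true difference.

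**Working it through.** **Inputs.** The protocol gives no rate for local skin events and none for rescue NPWT, so every such rate below is an illustrative assumption. Only the arm size comes from the plan (Sample size section).

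**1. Arm size.** 25% against 15%, two-sided 5%, 90% power, unpooled normal approximation: n = (1.960 + 1.282)² × (0.25×0.75 + 0.15×0.85) / 0.10² = 330.98, so 331 per arm, as stated. With 10% added, 331 × 1.10 = 364.1, and 2 × 364 = 728, as stated. I use 364 per arm except in step 4.

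**2. Endpoint counted in the NPWT arm only.** Assume 5% there: 0.05 × 364 = 18.2, taken as 18. Controls have 0/364 by definition. The odds ratio (18/346)/(0/364) is not finite. What can be reported is one proportion, 18/364 = 4.9% (Wilson 95% CI 3.2% to 7.7%), with no comparator.

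**3. Rescue NPWT in controls also counted.** Let r be the share of controls given a device and p the event rate per device recipient. The control rate is r×p, and OR = [p/(1−p)] / [rp/(1−rp)].

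| r | control events expected at p = 5% | OR, p = 2% | OR, p = 5% | OR, p = 10% |
|---|---|---|---|---|
| 5% | 0.91 | 20.4 | 21.0 | 22.1 |
| 10% | 1.82 | 10.2 | 10.5 | 11.0 |
| 20% | 3.64 | 5.1 | 5.2 | 5.4 |

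The result is close to 1/r by construction. It follows how often controls are rescued and hardly responds to how harmful the device is.

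**4. Control events recorded, but less completely.** Take 331 per arm, the same true 5% rate in both arms, full capture on NPWT and half capture on control. OR = (0.05/0.95)/(0.025/0.975) = 2.05. The chance of a false significant difference (Fisher exact, two-sided 5%) is 33%, against 3% with equal capture. So adding the items to the control form is not enough unless the times of assessment also match.

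**5. Same items, equally captured.** Half-width = 1.96 × √[p₁(1−p₁)/364 + p₀(1−p₀)/364].

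- 5% v 5%: difference 0 points (95% CI −3.2 to 3.2)
- 5% v 3%: 2.0 points (−0.8 to 4.8)
- 10% v 5%: 5.0 points (1.2 to 8.8)

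This is imprecise for small differences, but it is a comparison protected by randomisation, which steps 2 and 3 are not.

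**The case against.** A reader might infer that the protocol contradicts itself by planning an odds ratio that cannot be estimated. The text does not go that far. The Statistical analysis section does not name the primary safety endpoint. Its phrase about complications of the trial interventions can be read as meaning events counted in both arms, such as infection, dehiscence or reoperation, and for those the model works. Steps 2 and 3 are therefore conditional on the model being applied to the device endpoint. Step 3 also sits badly with a definition confined to the intervention group.

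A reader might also infer that the control arm will certainly collect nothing on local harms. The documents do not show that either. This is a journal article, the case report form is not shown, and such items may be on it. What can be said is that the stated definitions point to one arm and nothing stated extends them to the other.

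A third tempting inference is that harms in general go uncompared. They do not. Infection, dehiscence, seroma, haematoma, necrosis (including superficial necrosis), reoperations and readmissions are compared by arm. Wound-QoL and EQ-5D-5L are collected without arm restriction, and serious adverse events are defined without it. Maceration that progresses to one of the named wound complications is captured in both arms.

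Finally, recording faults that only a device can have in the device arm is a sound choice. All these objections stand and narrow the point. They do not remove it: a written one-arm rule for the primary safety endpoint remains, alongside a tolerability aim that needs two arms.

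**Conclusion.** The point holds in limited form. The primary safety endpoint and the recorded adverse events are tied to the NPWT device and arm, and no section states that blistering, maceration or skin reaction is recorded under the dry dressing. Following the text gives no fair randomised comparison of these harms.

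The gap covers minor local events that do not become a wound complication. Sample size, power and the primary efficacy conclusion are unaffected. Its numerical size cannot be derived from the document, and the odds ratios in the working show how the comparison would behave, not what to expect. The conclusion rests on reading the narrowing clause in the adverse-event section as meant, and on the unseen control form not already carrying these items. If it does carry them, only the wording and the timing of assessment need attention. The change is cheap and worth making, and it matters for the tolerability aim rather than for the trial's main result.

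**What to change.** - **Primary safety outcome and Potential adverse events related to intervention:** define one list of local dressing-related skin complications (such as blistering, maceration, skin reaction) for both arms. Record them with the same items at the same points: each dressing removal or change, and the end of the 14-day period. The common points matter because the NPWT device is reviewed daily, while most first dry dressings stay on for 48 hours to 5 days.
- **Comparison:** by randomised arm, for onset from surgery to day 14, with the model already planned. Day 14 covers all permitted allocated NPWT use and ends before rescue use in controls is offered. List later events separately.
- **Statistical analysis:** state that device-only problems (seal loss, premature removal) are reported as a proportion with a confidence interval among device recipients, including controls given one, and are left out of the between-arm odds ratio.

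The cost is wording in three sections and a few extra form items. The downsides are that attribution to the dressing is unblinded, late events need their own list, and the estimate is imprecise (about ±3 points at an assumed 5% in each arm). Dressing changes may still differ in number between arms, so the day-14 assessment is the one point sure to be common to both.
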